# Community Walks: a cluster randomized controlled trial of a multilevel physical activity intervention for low income public housing residents

**DOI:** 10.1186/s12889-023-16574-y

**Published:** 2023-08-31

**Keywords:** Physical activity, Walking groups, Multilevel intervention, Cluster randomized trial, Public housing

## Abstract

**Background:**

Physical activity behavioral interventions to change individual-level drivers of activity, like motivation, attitudes, and self-efficacy, are often not sustained beyond the intervention period. Interventions at both environmental and individual levels might facilitate durable change. This community-based study seeks to test a multilevel, multicomponent intervention to increase moderate intensity physical activity among people with low incomes living in U.S. public housing developments, over a 2 year period.

**Methods:**

The study design is a prospective, cluster randomized controlled trial, with housing developments (*n=*12) as the units of randomization. In a four-group, factorial trial, we will compare an environmental intervention (E) alone (3 developments), an individual intervention (I) alone (3 developments), an environmental plus individual (E+I) intervention (3 developments), against an assessment only control group (3 developments). The environmental only intervention consists of community health workers leading walking groups and indoor activities, a walking advocacy program for residents, and provision of walking maps/signage. The individual only intervention consists of a 12-week automated telephone program to increase physical activity motivation and self-efficacy. All residents are invited to participate in the intervention activities being delivered at their development. The primary outcome is change in moderate intensity physical activity measured via an accelerometer-based device among an evaluation cohort (*n=*50 individuals at each of the 12 developments) from baseline to 24-month follow up. Mediation (e.g., neighborhood walkability, motivation) and moderation (e.g., neighborhood stress) of our interventions will be assessed. Lastly, we will interview key informants to assess factors from the Consolidated Framework for Implementation Research domains to inform future implementation.

**Discussion:**

We hypothesize participants living in developments in any of the three intervention groups (E only, I only, and E+I combined) will increase minutes of moderate intensity physical activity more than participants in control group developments. We expect delivery of an intervention package targeting environmental and social factors to become active, combined with the individual level intervention, will improve overall physical activity levels to recommended guidelines at the development level. If effective, this trial has the potential for implementation through other federal and state housing authorities.

**Trial registration:**

Clinical Trails.gov PRS *Protocol Registration and Results System*, NCT05147298. Registered 28 November 2021.

## Background

Half of all U.S. adults do not participate in regular physical activity and women consistently report less activity than men [1, 2]. Among women, Latinas and Black women report the lowest rates of meeting physical activity guidelines compared to white women (40.5% and 36.1% versus 49.6%, respectively) and are disproportionately affected by chronic conditions such as diabetes and obesity [1, 3]. Many studies have consistently demonstrated a significant causal link between physical activity and health-related outcomes under controlled- and free-living conditions [4–9].

Evidence suggests that characteristics of the environments in which people live can facilitate or inhibit physical activity [10, 11]. Low-income neighborhoods are more resource poor for the promotion of physical activity compared to higher income neighborhoods, exposing residents to environments that fail to promote physical activity [12, 13]. Inadequate physical activity opportunities, lack of proximal retail businesses, poor neighborhood aesthetics, high crime, and heavy traffic are all characteristics of low-income neighborhoods that have been shown to deter physical activity [14–16]. The negative effects of environmental factors on physical activity and obesity are amplified if low-income areas are in urban zones [12]. The physical environment has also been associated with healthy physical activity in several studies; [17–19] for example, access and safety encourage walking trail use [20]. Overall, research suggests that the physical environment is a powerful influence on behaviors [21–23].

On the other end of the spectrum, individual level interventions delivered one-on-one can also be efficacious in changing physical activity behaviors [24, 25]. eHealth programs have particular benefits including convenience, scalability, and ability to deliver tailored messages. Indeed, individual level interventions can incorporate a range of behavioral change techniques when promoting physical activity, with one systematic review reporting that information about health consequences, behavioral goal setting, self-monitoring of behavior, and encouraging practical social support were the techniques most commonly included [26].

A limitation of past research is the under-recognition that individual-level programs may be most effective when delivered in environments that support and maintain the promoted physical activity changes, thus prompting calls for intervention programs that combine individual- and environmental-level changes [27–31]. This combination is in line with mainstay public health frameworks including the socio-ecological model in which behavior is conceptualized as being influenced by multiple levels ranging from individual, inter-personal, community, and policy [32]. Only a few published evaluations of multilevel interventions exist that measure changes in physical activity, with some trials on-going [33–36].

We propose to evaluate the effects of a multilevel community-based intervention package to increase moderate intensity physical activity using a cluster randomized design, using public housing developments as the unit of randomization. We expect that delivery of an intervention package targeted to the environmental and individual levels will improve overall physical activity levels to recommended guidelines at the housing development level [31].

## Methods/design

### Participants

The study setting is family-designated public housing developments in the City of Boston managed by the Boston Housing Authority (*N=*16) and other housing developments serving low-income populations managed by a private management company (*N=*26). Boston Housing Authority developments provide housing for nearly 13,000 low-income people who identify as white (9%), Black (33%), Hispanic (51%), or other (7%). Approximately two-thirds of adult residents are women. About 90% of residents speak English and/or Spanish. Prevalence of obesity and related health conditions are higher among individuals living in Boston's public housing developments compared to other city residents [37]. Approximately 62% of Boston public housing residents report insufficient physical activity [37] and, qualitatively, report environmental structural barriers to physical activity [38].

### Design of the Community Walks study

The design of this study, called Community Walks, is a prospective, cluster randomized controlled trial with housing developments as the unit of randomization. A total of 12 developments (8 managed by Boston Housing Authority and 4 privately managed) will be recruited to participate. Four arms will be compared: environmental intervention alone (E) (*n=*3 developments), individual intervention alone (I) (*n=*3 developments), environmental plus individual intervention (E+I) (*n=*3 developments) and an assessment only control group (*n=*3 developments). All intervention activities assigned to a particular development are available to all residents of that development.

To evaluate our outcomes, a subset of participants from each development will be recruited to serve in an evaluation cohort. The cohort will be assessed at baseline, at one-year, and at two-year follow-up time points. Primary and secondary outcomes will be assessed at these times. Baseline data collection is anticipated to finish at the end of 2023, and final results are expected in 2025. Community Walks has received approval from the Boston Medical Center/Boston University Medical Campus Institutional Review Board. When research staff learn of an adverse event, they report the event to the PI who then assesses details of the event and relatedness to study procedures and fulfills reporting requirements as necessary.

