##### Structured walking groups

HLAs will organize walking groups and adjust scheduling around work and childcare commitments of participants. Groups will begin meeting twice weekly and will occur more frequently as participation increases. The main recruitment strategies employed for these groups will be from flyers, from tables with posterboard displays, and by word-of-mouth referrals. Flyers will be distributed in a variety of ways including door-to-door, posting in high traffic areas, placing in mailboxes, and distributing at community events. Walk group participants will gather at a meeting place, such as a community room, within their development. Children are welcome to attend the walks with their parent/guardian to promote family participation and because improvised day care is not sustainable in the long run. Well behaved pets are also invited. All walking sessions will begin with light stretching. The groups then proceed with their walks. After each walk, they return to the meeting place for a post-walk stretching session. In case of inclement weather, all public housing developments have access to a large group room where they will lead indoor exercise classes, such as dance classes like Zumba or dances to upbeat popular music like Soca.

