#### Individual level intervention: automated ehealth phone program for physical activity

Phone2Health is based upon a previously tested telephone program designed to increase physical activity among urban African American adults [46] and was further modified to meet the needs of public housing residents (see section 2.3). Phone2Health is a 12-week automated telephone-based program, consisting of sessions lasting 10 minutes or less, available in English and Spanish. Enrolled participants will receive one call per week for 12 weeks with a goal of increasing motivation and self-efficacy for physical activity. The calls will include conversations that speak to participants using computer-controlled speech. The calls are user friendly and interactive where participants can respond to conversations by pressing keys on their phone’s keypad. Each week various barriers and recommendations are addressed through several sections of the call. Each week the call starts with a brief physical activity assessment to assess the participants current level of physical activity. Participants' level of physical activity will be based on the previous week's goal and their ability to meet or exceed that goal. The call moves into a counseling section where participants are given feedback from their assessment, information and tips on physical activity, and the benefits of incorporating physical activity into their lifestyle. Topics addressed in this section may include injury prevention, identifying support systems, or discovering different types of physical activity. Following the counseling section is goal setting, where each week participants set a new and achievable goal such as adding an additional day of physical activity during the week. Changes to goals are monitored by the system and the program will suggest an adjustment if the participant has chosen to increase the goal by a large amount or to decrease their goal. The call ends with a call summary and upbeat concluding statement, such as an inspirational quote. The program utilizes a “call-out” mechanism in which registered users receive a weekly call at a predetermined time and day.

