#### Individual-level measures: evaluation cohort

All eligible and consented participants will be sent a link to complete the surveys; if needed, the Research Assistant will administer surveys in person or over the phone. The Research Assistant will conduct the screening and baseline surveys and will also conduct the follow-up surveys at 12 months and 24 months for each enrolled participant. Standard socio-demographic measures will be assessed. All participants will receive a $40 pre-paid debit card at each completed assessment.

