#### Process measures

Process measures will be evaluated to monitor implementation of the intervention and to document receipt of the intervention. The HLAs will fill out a checklist after each physical activity event or promotion activity of the Phone2Health program. This information will help investigators determine intervention dosage and process. Specific metrics will include: 1) reach: the number of people who completed HLA walks/physical activity sessions or engaged in Phone2Health program; 2) the dose of the intervention: the number of HLA activities delivered and completed Phone2Health calls; and 3) participants’ feedback and perceptions of the intervention activities.

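### Adverse-event capture as described is passive and contact with study personnel differs by arm, so harm counts by arm could not be read as differences in risk

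*Protocol article*

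**What the plan says.** The handling of adverse events is set out in one sentence of the Protocol article, section Design of the Community Walks study: "When research staff learn of an adverse event, they report the event to the PI". The PI then looks into the event and its "relatedness to study procedures and fulfills reporting requirements as necessary".

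Contact that is common to all arms is the evaluation cohort's schedule: "The cohort will be assessed at baseline, at one-year, and at two-year follow-up time points". Table 1 (section Evaluation) lists what is measured at each of these times. It covers activity, mediators, moderators and process measures, and has no item on falls, injuries, safety incidents or adverse events.

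Other contact depends on the arm:

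- **E and E+I:** HLAs lead walking groups. "Groups will begin meeting twice weekly and will occur more frequently as participation increases" (section Structured walking groups). HLA training includes adverse events and first aid, and HLAs confer monthly with investigators (section Intervention overview: role of the HLA).
- **I and E+I:** "Enrolled participants will receive one call per week for 12 weeks" (section on the individual level intervention). The calls are automated. An HLA enrolls the resident and gets in touch after two weeks of missed calls.
- **Control:** the cohort assessments and nothing else.

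Walks are open to every resident of the development (section Design of the Community Walks study), and those who join need not give consent (section Environmental level intervention). Walkers therefore need not belong to the evaluation cohort.

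**The concern.** A rule that is triggered when staff learn of an event makes the record depend on how often staff are in a position to learn. That opportunity is tied to the randomized arm. A sprain on a group walk happens in front of a trained HLA. The same sprain in a control development reaches the study only if someone mentions it at an assessment, and no listed instrument prompts for it.

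The populations differ as well. Events seen at walks may involve residents outside the cohort, who have no counterpart in control and no defined denominator.

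This matters because the program encourages outdoor walking in low-income neighborhoods, for which the article's Background names crime and traffic as deterrents, and because the article hopes for adoption by federal and state housing authorities. Those bodies will ask whether the program is safe. An excess of events in E or E+I could be a product of observation, and a low count in control would say little.

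**Working it through.** The article gives no adverse-event rate, detection rate or harms comparison, so there is no stated figure to reproduce. The check has three steps.

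**1. Scheduled contact over two years.** At the starting frequency, and assuming that groups run throughout, an E or E+I development has 2 × 52 × 2 = 208 group sessions. Each cohort member in every arm has 2 assessments after baseline. The 208 is a count per development. It does not measure how often a given cohort member is seen, because attendance is voluntary and open to all residents.

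**2. Is there an equalizing measure?** Table 1 was read for anything asked alike in all arms that would record a harm. The nearest is the EQ-5D-3L, listed as a moderator at all three times. It describes health states, including pain or discomfort, and does not record events. Nothing in the table equalizes capture.

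**3. How large could the distortion be?** Suppose that true risk is the same in E and control. Let d0 be the probability that a control event is recorded, s the share of the E cohort who attend walks, and 0.95 the probability that an attendee's event is recorded. All three are assumptions. The value 0.95 is high, since it treats almost all of an attendee's events as noticed.

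Detection in E: dE = s × 0.95 + (1 − s) × d0. Ratio of recorded events: dE / d0.

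Example: d0 = 0.30 and s = 0.20 give dE = 0.20 × 0.95 + 0.80 × 0.30 = 0.43, and 0.43 / 0.30 = 1.43.

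| d0 | s = 5% | s = 20% | s = 50% | s = 100% |
|---|---|---|---|---|
| 0.30 | 1.11 | 1.43 | 2.08 | 3.17 |
| 0.60 | 1.03 | 1.12 | 1.29 | 1.58 |
| 0.90 | 1.00 | 1.01 | 1.03 | 1.06 |

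In counts: each arm has 3 × 50 = 150 cohort members. With an assumed true risk of 5% there are 150 × 0.05 = 7.5 true events per arm. At d0 = 0.30, control records 7.5 × 0.30 = 2.25. E records between 7.5 × 0.3325 = 2.5 (s = 5%) and 7.5 × 0.95 = 7.1 (s = 100%). With an assumed 10% risk these figures double.

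The distortion is negligible when control events are mostly recorded or few cohort members walk, and about threefold at the other extreme. The article fixes neither input. Events among walkers outside the cohort are not in this calculation and would add to the E and E+I counts only.

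**The case against.** The strongest reply is that this is a journal article. It cites a full protocol, version 1.8, which is not shown, and event forms and visit scripts belong there. One sentence on the reporting chain does not exclude asking about events at the 12- and 24-month contacts. This stands as a limit: the point concerns the rule as described, and a reader should not infer that events are recorded only when staff come across them. It does not dispose of the point. The article states a trigger and sets out its measures at each time point, and the two together describe passive capture.

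A reader might also infer that control residents meet no staff, since "All eligible and consented participants will be sent a link to complete the surveys". The text that follows does not support this: the Research Assistant conducts the 12- and 24-month surveys for every participant, and the accelerometer is worn at those times in all arms. Nor is the I arm without human contact, since HLAs enroll residents and follow up missed calls. The contrast is one of degree.

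A reader might further infer that a resident who stops a walk injured is lost to the safety record, because one process metric is "reach: the number of people who completed HLA walks/physical activity sessions or engaged in Phone2Health program". That metric measures engagement. It is not the adverse-event route, and nothing about harms follows from it.

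It is also unclear whether HLAs count as research staff, since the Analysis plan names study staff and HLAs separately. If they do not, what they notice would reach the record less directly, though their adverse-event training and monthly contact with investigators make some transfer likely.

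Finally, harms are not an outcome and the aims contain no between-arm comparison of them. This stands in full.

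**Conclusion.** The point holds in limited form. Capture as described is passive, no listed measure asks all arms about harms, and contact is greater in E and E+I than in I or control. A by-arm count of harms could be biased toward more recorded events in E and E+I, and could not be separated from true risk.

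Two stronger readings are not supported. A reader might infer that recorded harms will be far higher in the walking arms. The article gives neither attendance nor detection, and the assumed inputs give ratios from about 1.0 to about 3. A reader might also infer that any excess would have nothing to do with true risk. Walking and exercise sessions may themselves change risk, and the difficulty is that the two explanations cannot be told apart.

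The primary and secondary efficacy analyses are untouched. This is an inexpensive improvement to what the trial can say about safety, and it does not threaten the main results.

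**What to change.** Three changes:

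1. Add the same short harm items to the existing 12- and 24-month cohort surveys in all four arms: any fall, injury or safety incident since the last assessment, and whether care was sought. Do not limit them to study activities, because such wording would depend on exposure to the intervention.
2. Base any between-arm statement on harms on these items only.
3. Report events noticed by HLAs at walks separately and descriptively, distinguishing cohort members from other residents where this is known.

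If the full protocol already asks all arms the same question, one sentence saying so is enough.

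The cost is a few items in surveys that are already given and a minor IRB amendment. The surveys become slightly longer. Recall runs over 12 months and may itself differ by arm, because residents know which activities they are offered, so the items narrow the imbalance without removing it. Participants already past month 12 would have the items at month 24 only. Recruitment began on May 2, 2022 and the protocol version is dated June 7, 2023, so at that date this applied only to people enrolled in roughly the first five weeks.

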### Formative research

From August 2020 to February 2021, we conducted four videoconference meetings with our established community advisory board comprised of Spanish- and English-speaking residents from Boston public housing developments. The first meeting was used to introduce the individual-level telephone physical activity program and ask members to elaborate on what they see as barriers to physical activity among public housing residents and to comment on barriers previously identified in the literature (e.g., lack of time, familial influences and responsibilities, lack of basic knowledge related to physical activity, lack of transportation, lack of resources and inadequate places to participate in physical activity, increased fatigue and lack of energy, and barriers related to body image). We also shared potential message content and asked for feedback on message acceptability and desired changes. In subsequent meetings, we provided revised content and received further feedback. Overall, members suggested simplifying information and sentence structure to aid understanding. They offered tips for making the telephone content more engaging, and suggested ways to recruit participants in their developments. We incorporated these suggestions into script development. Scripts were developed in English, translated into Spanish, and then reviewed and revised for cultural appropriateness by two bilingual team members. Meetings of the community advisory board continued to occur 2-3 times a year to provide updates and obtain feedback on study progress.

